## Abstract

**Background:**

Success rates with conventional transvenous endocardial pulmonary vein isolation in patients with persistent and longstanding persistent atrial fibrillation (AF) are variable due to advanced electrical and structural remodeling of the atria. As a consequence, more extensive endocardial lesions, minimally invasive thoracoscopic surgical techniques, and hybrid ablation (combining thoracoscopic epicardial surgical and endocardial catheter ablation) have been developed.

**Hypothesis:**

The HARTCAP-AF trial hypothesizes that hybrid AF ablation is more effective than (repeated) transvenous endocardial catheter ablation in (longstanding) persistent AF, without increasing the number of associated major adverse events.

**Methods:**

This randomized controlled trial will include 40 patients with persistent or longstanding persistent AF who will be 1:1 randomized to either hybrid ablation or (repeated) catheter ablation. The procedures and follow-up are conducted according to the guidelines. The primary effectiveness endpoint is freedom from any supraventricular arrhythmia lasting longer than 5 min without the use of Vaughan-Williams class I or III antiarrhythmic drugs through 12 months of follow-up after the last procedure. In the catheter ablation arm, a second procedure planned within 6 months after the index procedure is allowed for obtaining the primary endpoint. Additionally, adverse events, cost-effectiveness, and quality of life data will be recorded.

**Trial registration:**

ClinicalTrials.gov, NCT02441738. Registered on 12 May 2015.

**Electronic supplementary material:**

The online version of this article (10.1186/s13063-019-3365-9) contains supplementary material, which is available to authorized users.

## Background

Transvenous endocardial catheter ablation for pulmonary vein isolation (PVI) is the standard treatment option for patients with symptomatic paroxysmal atrial fibrillation (AF). Unfortunately, single procedural results of this technique in (longstanding) persistent AF are less convincing [1–5]. Due to advanced electrical and structural remodeling in these patients with nonparoxysmal AF, a more extensive lesion set might be required to achieve rhythm control. Multiple techniques have been introduced, including ablation of complex fractionated atrial electrograms (CFAE) [4–6], the application of linear lesions [4, 7–9], rotor ablation [10], or a combination of techniques in the so-called stepwise approach [11–15]. However, reported results are highly variable. One of the major limitations seems to be the availability of percutaneous devices able to reliably create transmural lesions [16].

While surgical techniques have proven to be more efficacious in overcoming this limitation [17], approaches such as the Cox-Maze procedure are considered too invasive and complex and therefore have never been widely adopted. This has led to the development of minimally invasive thoracoscopic surgical techniques and hybrid ablation. In hybrid ablation, consisting of a combination of thoracoscopic epicardial surgical and endocardial catheter ablation, surgeons and electrophysiologists combine their expertise to maximize success rates and minimize procedural complications [18]. However, the question of which lesion sets should be used in patients with nonparoxysmal AF remains unanswered. The HRS/EHRA/ECAS expert consensus statement [19] and the guidelines of the Society of Thoracic Surgeons [20] recommend considering additional ablation lesions besides PVI, but do not specify which strategy to use due to a lack of evidence. Therefore, research to identify the most appropriate lesion set and ablation technique is critical to improve results in these patients.

Currently, there is lack of clinical data comparing different ablation strategies in the treatment of nonparoxysmal AF. It is the aim of the present study to compare the safety, efficacy, and cost-effectiveness of hybrid ablation (performed in one stage) versus transvenous endocardial catheter ablation (allowing repeated ablation procedures).

## Methods

### Design and hypothesis

This is a prospective, randomized trial conducted at the Maastricht University Medical Centre, Maastricht, the Netherlands. The study objective is to compare the efficacy and safety of two interventional approaches for symptomatic, drug refractory persistent or longstanding persistent AF. A total of 40 eligible patients will be randomized (in a 1:1 ratio) to the following treatment arms: 1) a hybrid ablation arm (*n* = 20 patients), a one-stage hybrid procedure consisting of surgical thoracoscopic epicardial ablation combined with endocardial catheter ablation; or 2) a catheter ablation arm (*n* = 20 patients), consisting of conventional endocardial catheter ablation, followed by repeated catheter ablation if clinically indicated and decided within 6 months after the initial procedure.

The primary and secondary effectiveness endpoints are shown in Table 1. A blanking period of 3 months is applied. A second ablation after the hybrid ablation and a decision for redo-ablation beyond 180 days after the index catheter ablation will be considered a failure. A third catheter ablation at any time will also be considered a failure in the catheter arm. While the current guidelines define failure as a recurrence of > 30 s, failure in the primary endpoint of this study is defined as a recurrence of > 5 min [19, 21]. This allows us to reliably evaluate various Holter examinations and this reflects a more clinical endpoint compared with > 30 s, since it has been shown that the presence of AF episodes >30 s do not predict clinically meaningful AF, and that quality of life is mainly negatively influenced in patients with a high symptomatic AF burden [22, 23]. The primary and secondary safety endpoints are shown in Table 2.

**Table 1 Tab1:**
[figure not shown]
Effectiveness endpoints

**Table 2 Tab2:**
[figure not shown]
Effectiveness endpoints

This study hypothesizes that a one-stage hybrid ablation will have greater clinical effectiveness during long-term follow-up compared with (repeated) endocardial catheter ablation in patients with (longstanding) persistent AF, without increasing the number of associated major adverse events.

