### Sample size calculation

The estimated success rate (freedom from any supraventricular arrhythmia lasting > 5 min without the use of Vaughan-Williams class I or III AAD through 12 months of follow-up after the last procedure) based on literature and our own clinical experience is 35% for single catheter ablation [2, 29] and 83% for a hybrid ablation [30, 31]. With a significance level of α = 0.05, and a power of 90%, 20 patients per group need to be included.

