### Statistical analysis

Data analysis on the final dataset will be performed using SPSS statistical software. The per-protocol principle will be used since patients who withdraw consent before the ablation has taken place are excluded from the analysis. Univariate analysis will be applied to both continuous (*t* test or nonparametric tests) and categorical variables (Chi-square test). Continuous variables will be reported as the mean ± standard deviation (for normally distributed variables) or median/p10–p90 (for not normally distributed variables), and categorical variables will be reported as the observed number and corresponding percentage. Depending on the number of events, univariate (*t* test or Chi-square) or multivariate analysis (logistic regression) will be used to explore the relationship between baseline covariates and post-baseline endpoints. Kaplan-Meier survival curves will be plotted. All necessary decisions with regards to power calculations for secondary endpoints are made blind. Missing data are not computed or imputed, and the participant will be excluded for the analysis which involves the missing data.

For the cost-effectiveness analysis, any missing data will be imputed using a multiple imputation approach. As most volumes of resource use follow a skewed distribution, differences between the two groups will be analyzed with bias-corrected bootstrap analysis. In addition, bootstrap analysis will also be used to quantify the uncertainty surrounding the incremental cost-effectiveness ratio. Results of this analysis will be presented in cost-effectiveness planes and acceptability curves. Sensitivity analysis will be performed to estimate, for example, the impact of parameters on the incremental cost-effectiveness ratio. Discounting will be applied for both costs (4%) and effects (1.5%).

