
One reason for the inconsistent results and high failure rates might be the limitations of the devices used to create transmural lesions. For example, in the STAR-AF II trial standard unipolar endocardial uniparietal catheter techniques were used, which are known to not reliably produce long-lasting transmural lesions [38]. Incomplete linear lesions can be arrhythmogenic due to the possibility for re-entry at the site of gaps or by changing conduction velocity [39]. However, even if current state of the art technology is applied, as in the recent Fire and Ice trial, the limitations of endocardial ablation in reliably creating transmurality currently still remain evident [40]. Surgical bipolar and biparietal devices are better at creating transmural lesions, and modern technologies allow for an anatomical approach using thoracoscopic visualization. However, epicardial surgical ablation is unable to create efficacious isthmus lesions and lacks the opportunity of sophisticated high-density three-dimensional mapping and consecutive endocardial touch-up of gaps. A hybrid ablation, which encompasses all of these opportunities, can lead to single-procedure success rates of more than 85% freedom from AF without AADs [18, 30, 31].

Besides efficacy in terms of rhythm control, safety also determines if an approach can be recommended. The advantages of catheter ablation are that full sedation is not needed, the duration of admission is short, and recovery is fast. The complication rates of this procedure vary from 0.2% to 4% per complication, with a cumulated complication risk of 7.7% to 13% [32, 41], which we have confirmed in our center. A hybrid ablation gives a total minor complication rate of 4% and total major complication rate of 5% [42]. In our center, we have confirmed these reported complication rates [30].

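### The hypothesis of no increase in major adverse events cannot be supported by 20 patients per arm sized on efficacy alone, and a non-significant safety comparison could be misread as no increase

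*Protocol article*

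**What the plan says.** The Hypothesis paragraph of the Abstract and the text after Table 2 in Methods both give the hypothesis two parts: greater effectiveness with hybrid ablation, "without increasing the number of associated major adverse events". Design and hypothesis also lists safety in the study objective and refers to Table 2 for primary and secondary safety endpoints. The content of that table is not visible in the copy reviewed.

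On size, Design and hypothesis says: "A total of 40 eligible patients will be randomized (in a 1:1 ratio"), that is, 20 per arm. Sample size calculation rests this on success rates alone. The expected rate "is 35% for single catheter ablation [2, 29] and 83% for a hybrid ablation [30, 31"], and then: "With a significance level of α = 0.05, and a power of 90%, 20 patients per group need to be included".

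Statistical analysis names one between-arm test for "categorical variables (Chi-square test"). It adds that decisions on power for secondary endpoints are taken blind, but gives no figure.

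On expected event rates, the Discussion says "A hybrid ablation gives a total minor complication rate of 4% and total major complication rate of 5" per cent. For catheter ablation it reports individual complications, "with a cumulated complication risk of 7.7% to 13" per cent, without separating major from minor.

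**The concern.** A claim of no increase has to rule out an excess. A difference test that fails to reject does not do that, least of all in a trial whose size was set by a 48-point effectiveness difference (83% minus 35%) and which expects only one to three patients with events per arm. The hypothesis already contains the sentence that a results paper might use: more effective, with no more major adverse events. If the second half came to rest on a non-significant p-value, it would rest on lack of information.

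The question matters because one arm adds thoracoscopic surgery. The evidence in the Discussion is mixed. It cites a randomized trial in which surgical (not hybrid) ablation had more adverse events than catheter ablation, and a retrospective study of 166 patients with no significant difference in complications.

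**Working it through.** **1. The plan's own figure.** With p1 = 0.35, p2 = 0.83, mean 0.59, two-sided α = 0.05 (sidedness is not stated) and power 90%:

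n = [1.960·√(2·0.59·0.41) + 1.282·√(0.35·0.65 + 0.83·0.17)]² / 0.48² = 4.585 / 0.2304 = 19.9, so 20 per arm.

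The stated number reproduces. It contains no safety input.

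**2. Expected patients with events among 20.**
- Hybrid, major: 20 × 0.05 = 1.0.
- Catheter, all complications cumulated: 20 × 0.077 = 1.5 to 20 × 0.13 = 2.6.

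The catheter major rate is not given. I take 5% as an assumption and use 7.7% and 13% to show the range.

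**3. Power of the Chi-square test to detect a true rise.** Exact enumeration of all 21 × 21 outcomes, two independent binomials with n = 20, uncorrected Pearson test, p < 0.05. The hybrid rates are assumed scenarios.

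| Catheter | Hybrid | Power |
|---|---|---|
| 5% | 10% (doubling) | 5% |
| 5% | 15% | 15% |
| 5% | 20% | 29% |
| 5% | 40% | 82% |
| 7.7% | 15.4% (doubling) | 10% |
| 13% | 26% (doubling) | 18% |

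From 5%, about an eightfold rise is needed before power reaches roughly 80%. In counts, with one catheter event the hybrid arm needs 6 of 20 for p < 0.05 (6 v 1: p = 0.037; 5 v 1: p = 0.077).

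**4. What the interval would say.** Newcombe 95% interval for the risk difference, built from Wilson limits. For 1/20 the Wilson limits are 0.0089 and 0.2361. With 1/20 in each arm:

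0 ± √[(0.05 − 0.0089)² + (0.2361 − 0.05)²] = ± 0.191, or −19 to +19 points.

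- 0/20 in each arm: −16 to +16 points.
- 3/20 hybrid v 1/20 catheter: −11 to +31 points.
- One arm with 0/20: exact upper limit 1 − 0.025^(1/20) = 16.8%.

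**5. What ruling out an excess would take.** The article gives no margin, so the margins m are assumptions. With both arms at 5%, one-sided 0.025 and power 80%:

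n per arm = (1.960 + 0.842)² × 2 × 0.05 × 0.95 / m²

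This gives 299 (m = 5 points), 75 (10), 34 (15) and 19 (20). Twenty per arm therefore suffices only at about 20 points, four times the quoted 5% rate. At a 10-point margin, power with 20 per arm is about 31%. If hybrid is at 5% and catheter is truly worse, it is 38% (catheter 7.7%) or 52% (catheter 13%).

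**6. Does the Chi-square test itself misbehave here?** With equal rates in both arms, its true size at nominal 5% is 1.2% (rate 5%), 2.7% (7.7%), 3.9% (10%) and 4.7% (13%). It is conservative and does not produce excess false positives. Fisher's exact test is more conservative still: its power is 7% for 5% v 15% and 17% for 5% v 20%, against 15% and 29%.

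**The case against.** Four objections have force.

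- **No misuse is documented.** A reader might infer that the investigators will report a non-significant result as equal safety. Nothing in the article says so. The objective speaks neutrally of comparing efficacy and safety, and the hypothesis is not set up as a non-inferiority test. The point must be that the result could be misread.
- **The Chi-square test is named generically.** It stands for categorical variables at large and not specifically for the safety endpoints, and Table 2 cannot be seen. That stands. It is still the only categorical comparison stated, and the interval widths in step 4 do not depend on it.
- **A margin, a confidence-interval rule or a sparse-table method may be in the full protocol or analysis plan.** That stands too, so the absence of a margin here is not the finding. The sample size is fixed in this article, however, and no analysis can make 20 per arm informative enough to exclude a moderate excess at these rates.
- **The 5% rate belongs to the hybrid arm only.** A reader might apply it to both arms as the article's own expectation. The Discussion does not support that, because the catheter figure is cumulated over complications of all severities. The range from 5% to 13% in step 3 shows that low power does not depend on the assumption.

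It is also tempting to say that sparse cells make the Chi-square test invalid and that Fisher's test should replace it. Step 6 does not support this: the change would roughly halve the power to detect harm in the two scenarios shown.

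**Conclusion.** The point holds as a mismatch within the article. Half of the stated hypothesis is a no-increase claim, while the design is sized for effectiveness alone and the stated categorical comparison is a difference test. Under an assumed 5% catheter major rate, a tripling would be missed about 85% of the time (1 − 0.15) and a quadrupling about 71% (1 − 0.29). Power to detect a doubling stays at or below about 18% for baseline rates from 5% to 13%. Equal counts of one event per arm would still be compatible with an excess of 19 points.

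The arithmetic is firm given these rates. The scenarios for the true hybrid rate and the margins are my assumptions. The documents do not support going further, to say that equal safety will be claimed or that the Chi-square test inflates error here. This should be changed because it affects what the trial may conclude on safety; it does not affect the effectiveness comparison.

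**What to change.** - Confine the confirmatory hypothesis to effectiveness, in the Abstract and in Methods.
- Make safety an estimation objective, using the safety endpoints already set out in Table 2. I propose no new endpoint definition, since that table is not visible.
- Report each arm with an exact or Wilson 95% confidence interval, and the risk difference with a Newcombe or score 95% interval.
- State in advance that a non-significant difference will not be reported as no increase in major adverse events.
- Do not change to Fisher's test for this purpose, because it lowers the power to detect harm. The intervals should carry the interpretation.

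The cost is wording and a few lines of analysis, with no extra patients. The downside is a more modest safety claim. Keeping a confirmatory no-increase claim would instead need a prespecified margin and a sample size built on it: with both arms at 5% and 80% power, 75 per arm at an assumed 10-point margin.

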### Inclusion criteria

All patients (male and female, aged > 18 years, mentally able and willing to give informed consent) with symptomatic persistent or longstanding persistent AF refractory or intolerant to at least one Vaughan-Williams class I or III antiarrhythmic drug (AAD) who are able and willing to receive all of the study-related procedures are eligible for enrolment in this trial.

### Exclusion criteria

Potential subjects will be excluded from the study if any of the conditions shown in Table 3 apply.

**Table 3 Tab3:**
[figure not shown]
Exclusion criteria

### Randomization

Randomization will be performed directly after written informed consent is obtained by the Clinical Trial Center Maastricht using the ALEA software program (FormsVision BV, Abcoude, the Netherlands). This software is programmed to equally distribute the number of patients over the two groups so that an even number of patients are treated with either catheter or hybrid ablation. The randomization is block designed and restricted (stratified); the type of AF (persistent or longstanding AF) will be taken into account to ensure a good balance of patient characteristics in both groups. Using this randomization method, allocation concealment is guaranteed. For every patient that withdraws their consent before the ablation is performed, an additional patient will be randomized.

### Pre-procedural investigations

Pre-procedural investigations include physical examination, 12-lead electrocardiogram (ECG), blood analysis (e.g., hemoglobin, C-reactive protein, creatinine), transthoracic echocardiography, a lung function test, and a standard computed tomography (CT) scan. Patients older than 60 years and patients with an elevated cardiovascular risk profile (i.e., family history of cardiovascular disease, elevated body mass index, diabetes, dyslipidemia, hypertension, or smoking) will undergo a cardiac CT scan or coronary angiogram. In addition, quality of life (using the EQ-5D-5 L questionnaire) is assessed at baseline.

### Intervention: transvenous catheter ablation

This ablation procedure is conducted while the patient is under sedation or general anesthesia. At the beginning of the procedure, a transesophageal echo is performed to confirm the absence of intracardiac thrombi. A His bundle (St. Jude Medical, St. Paul, Minnesota) and coronary sinus catheter (Medtronic, Minneapolis, Minnesota) are placed under fluoroscopy. Access to the left atrium is achieved via a femoral approach and double transseptal puncture. A single bolus of 100 IU/kg bodyweight of heparin is administered, followed by a heparin perfusor to maintain an activated clotting time above 300 s. An electroanatomical map of the left atrium is created using a mapping catheter (Lasso or Pentaray, Biosense Webster, Diamond Bar, California) with direct visualization on a three-dimensional mapping system (Carto, Biosense Webster). The ablation is performed using an irrigated tip contact force radiofrequency (RF) ablation catheter (ThermoCool Smarttouch, Biosense Webster). Automated lesion tagging (VisiTag, Biosense Webster) is used to mark the location of each ablation lesion. The power setting used is 25–30 W with an ablation index of 400 at the posterior wall, and 30–35 W with an ablation index of 500 at the anterior wall and other regions of the left atrium. The minimum lesion set that has to be performed is PVI and a superior and inferior connecting line (box lesion) (Fig. 1). In cases of a documented right atrial flutter (AFL), AFL induced during the ablation, or a dilated right atrium (> 25 mL/m^2^ in men, > 21 mL/m^2^ in women), a cavotricuspid isthmus (CTI) line is performed. Additional ablation lesions might be performed at the electrophysiologist’s discretion. Complete isolation (entrance and exit block) of all pulmonary veins and the box lesion, and completeness of additional ablation lines, must be electrophysiologically confirmed. If the patient is still in AF at the end of the procedure, the patient is electrically or pharmacologically cardioverted.

**Fig. 1 Fig1:**
[figure not shown]
Box lesion in the setting of catheter ablation. Carto image showing a view of the posterior wall of the left atrium after wide area circumferential ablation of the pulmonary veins, and a connecting roof and inferior line (pink and red dots)

In the event of an eventual second study ablation, the lesions made in the initial ablation are checked for conduction gaps and re-ablated as needed. Additional lesions are added, if necessary, at the electrophysiologist’s discretion.

### Intervention: hybrid ablation

At the beginning of this procedure a transesophageal echo is performed to confirm the absence of intracardiac thrombi. Surgical epicardial ablation is performed while the patient is under general anesthesia, with double-lumen endotracheal intubation using video-assisted thoracoscopic surgery on the beating heart. Access is gained through small incisions in the intercostal spaces. On the right side, the pericardial sac is opened parallel and ventral to the phrenic nerve. The pericardial reflections around both caval veins are dissected to provide access to the transverse and oblique pericardial sinuses. The right pulmonary veins are isolated using a bipolar RF clamp (Synergy System, AtriCure Inc., Cincinnati, OH, USA). The right-sided parts of the superior and inferior line are created using a bipolar unidirectional RF device (Coolrail, Atricure Inc., Cincinnati, OH, USA). On the left side, a similar procedure is performed. This box lesion is the epicardial lesion set in all patients regardless of their type of AF (Fig. 2). The right-sided thoracoscopic approach can be omitted if complete right pulmonary vein isolation and box lesion can be safely performed with a left-sided thoracoscopic approach only. In case of a CHA_2_DS_2_-VASc ≥ 1, closure of the left atrial appendix (LAA) using an epicardial Atriclip device (Atricure Inc., Cincinnati, OH, USA) is performed.

